### Additional Scales

In addition to the brief MIOS or MIOS-4 and the SUDS, the scales in the following sections will be included on the web-based platform.

#### GAD Scale

The GAD Scale [40] is a measure that assesses the level of anxiety a person has experienced over the last 2 weeks. The scale consists of 7 items, with each item scoring on a Likert scale of 0 to 3. The total score ranges from 0 to 21, with higher scores indicating greater anxiety. The GAD-2 only includes items 1 and 2 of the GAD-7 and has a total score that ranges from 0 to 6.

#### PHQ Scale

The PHQ [41] is a self-report questionnaire assessing symptoms of depression over the last 2 weeks. The PHQ-9 scale consists of 9 items, with each item scoring on a 4-point Likert scale from 0 (not at all) to 3 (nearly every day). The total score ranges from 0 to 27, with higher scores indicating more severe symptoms of depression. The PHQ-2 includes only the first 2 items of the PHQ-9 and has a total score range of 0 to 6.

#### UCLA 3-item Loneliness Scale

The UCLA 3-item Loneliness Scale (UCLA-3) [55] is a self-report questionnaire assessing subjective feelings of loneliness and social isolation. This scale consists of three items, with each item scoring from 1 (hardly ever) to 3 (often). The total score ranges from 3 to 9, with higher scores indicating more severe symptoms of loneliness.

Scales will be administered 3 times per week, according to the schedule shown in Table 1.

**Table 1 table1:** Scale administration schedule.

Day	Scale
Monday	SUDS^a^ GAD-2^b^ PHQ-2^c^ MIOS-4^d^ UCLA-3^e^
Thursday	SUDS GAD-2 PHQ-2 MIOS-4 UCLA-3
Saturday	SUDS GAD-7^f^ PHQ-9^g^ Brief MIOS^h^

^a^SUDS: Subjective Units of Distress Scale.

^b^GAD-2: Generalized Anxiety Disorder-2.

^c^PHQ-2: Patient Health Questionnaire-2.

^d^MIOS-4: Moral Injury Outcome Scale-4.

^e^UCLA-3: UCLA 3-item Loneliness Scale.

^f^GAD-7: Generalized Anxiety Disorder-7.

^g^PHQ-9: Patient Health Questionnaire-9.

^h^Brief MIOS: Brief Moral Injury Outcome Scale.

### Engagement Strategy

We will use several new strategies to maximize participant engagement. First, we will send daily SMS text messages reminding participants to use their wearable and to open the wearable app. The text messages will also include a reminder on Mondays, Thursdays, and Saturdays to complete the questionnaires. Second, we will send emails reminding participants on Mondays, Thursdays, and Saturdays to complete the questionnaires. Third, we will actively monitor which participants are missing data and contact those who are on a weekly basis. Different actions will be taken depending on the amount of missing data, which are outlined in Table 2.

Lastly, we will establish a compensation system to further encourage compliance. For every 2-week period following their VR session, participants will be compensated CAD $30 (US $21.93) if they did not go a single day without any missing active or passive data. Participants will be given this honorarium upon completing the study. Participants will also be given CAD $80 (US $58.48) for completing the screening visit, CAD $80 for the VR visit, and CAD $30 for the exit interview (see Exit Interview section).

**Table 2 table2:** Engagement action according to the amount of missing questionnaire and wearable data received.

Severity level	Amount of missing data	Engagement action
Minor	Missing at least one day of questionnaires or one day of wearable data in a week.	Call participant and ask them to contact the research team if they are having technical difficulties.
Medium	Missing one or 2 days of questionnaires, 2 weeks in a row; 2 questionnaires in one week; or wearable data 3 days a week, 2 weeks in a row.	Call and text participants, ask them to contact the research team regarding their missing data regardless of whether there are no technical difficulties. Repeat contact daily until response is established.
Major	Missing questionnaire 3 days in a week; wearable 4 days or more in a week; or at least 3 days of wearable data in addition to one day of questionnaires per week.	Call and text participants, ask them to contact the research team regarding their missing data regardless of whether there are no technical difficulties. Repeat contact daily until response is established.

### Debrief

The debrief, which will take place immediately after the VR session, will be composed of a semistructured interview, open-ended feedback, and 3 Likert-rated statements (an interview guide is included in Multimedia Appendix 3). The semistructured interview will ask participants to reflect on and explore emotions elicited by the VR simulation and will test participants’ retention of the material from the educational video. Open-ended feedback and Likert-rated statements will explore participants’ impressions of the VR simulation and how it could be improved and made more realistic.

### Exit Interview

At the end of the 12-week follow-up period, participants will complete a semistructured exit interview regarding their experience in the study, including perceptions of the utility and relevance of the educational video and barriers to the use of digital platforms (an interview guide is included in Multimedia Appendix 4). Included in this interview will be a retention test on the concepts and strategies discussed in the educational video. After the interview, the participant will complete the User Experience Questionnaire for the wearable and web-based platform. The User Experience Questionnaire is a widely used questionnaire for measuring impressions of the user experience of interactive products [56,57].

### Quantitative Data Analysis

#### Sample Size

This project aims to demonstrate the preliminary utility of multimodal digital platforms to understand and mitigate general stress and moral distress. Sample size calculations were estimated based on the results of a post hoc analysis of a pilot study [33].

We calculated sample sizes for a 2-tailed paired *t* test to compare the means of the prescore and postscore of MIOS using the POWER procedure in SAS (version 9.4; SAS Institute). Parameters for the sample size calculation were estimated from a pilot study, as the SD of each score was 9.86 and the correlation of pre- and postscores was 0.75. A sample size of 55 pairs (55 patients) was estimated with a 2-sided α of 5% and a power of 90%. We set the effect size (mean difference between prescore and postscore) to detect at 3.13. Therefore, assuming a conservative dropout rate of 30%, the proposed sample size of 100 patients will still provide 70 pairs, which is sufficient to achieve >90% power based on the parameter assumptions.

#### Statistical Analysis

R (R Core Team) and SAS will be used to conduct statistical analysis. General participant characteristics and demographics will be listed in a baseline characteristics table. Continuous variables will be presented with the mean and SD when normally distributed, or with the median and IQR for skewed data. Dichotomous and categorical variables will be presented with frequency and percentage.

For the brief MIOS and other scales from the VR session (eg, MIOS-4 and SUDS), the prescore, postscore, and their differences will be summarized using descriptive statistics such as mean (SD) and median (IQR). For each scale, the prescore and the postscore will be compared using 2-tailed paired *t* tests. Similar analyses will be performed for the scales in the web-based platform (eg, GAD-7, GAD-2, PHQ-9, PHQ-2, and UCLA-3). The normality of all scale data will be assessed using a Shapiro-Wilk test to validate the use of the 2-tailed paired *t* test, which assumes normality. If the normality test indicates a significant deviation from a normal distribution, the Wilcoxon signed rank test, a nonparametric test for paired data, will be used. Results will be considered significant with a *P* value ≤0.05.

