## Discussion

### Potential Benefits

Participants may benefit from psychoeducation related to stress, moral distress, and techniques to address those experiences. Participants may also experience some degree of relief from moral distress throughout this study from the educational video, and the opportunity to better understand their mental and physical health through self-monitoring built into the web-based and wearable platforms. Further, participation in this study can benefit nursing professionals as a whole, contributing to the understanding and prevention of stress and moral distress in health care professions.

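### Web-platform scales measured 14 to 42 times per participant are tested by a pre/post paired comparison with no time term, so most occasions go unused and background change would count as a VR effect

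*Protocol article*

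**What the plan says.** In the protocol article, the Statistical Analysis section states for each VR-session scale that "the prescore and the postscore will be compared using 2-tailed paired" t tests, with the Wilcoxon signed rank test as fallback if normality is rejected. It then says "Similar analyses will be performed for the scales in the web-based platform" and lists GAD-7, GAD-2, PHQ-9, PHQ-2 and UCLA-3 as examples. The threshold is common to all: "Results will be considered significant with a *P* value ≤0.05". No other inferential analysis of these scales is named, and pre and post are not defined for them.

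The schedule is dense. "Scales will be administered 3 times per week, according to the schedule shown in Table 1": SUDS on all three days; GAD-2, PHQ-2, MIOS-4 and UCLA-3 on Monday and Thursday; GAD-7, PHQ-9 and brief MIOS on Saturday. Trial Design sets a baseline of at least 2 weeks, and the Web-Based Platform section a 12-week follow-up. The short forms are subsets of the long ones; for example, "The GAD-2 only includes items 1 and 2 of the GAD-7".

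The Abstract presents the pre-post comparison as the analysis of the VR intervention's effects, and Objectives says the repeated measures serve to monitor the effects of the VR session. Potential Benefits also names "self-monitoring built into the web-based and wearable platforms" as a possible source of relief. Limitations admits that there is no control group, but explains the consequence only for the first against the second simulation run.

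**The concern.** A pre/post paired test suits the VR session, where each scale has a few fixed administrations. Carried over to a 14-week series, it has three weaknesses.

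- **Unused data.** If one baseline score is set against one follow-up score, the remaining occasions play no part in the effect test.
- **Incomplete pairs.** A paired test drops anyone who lacks either score. The Introduction reports poor engagement in phase 1, and Sample Size works from "assuming a conservative dropout rate of 30" percent.
- **No time term.** Any change over the interval, whether seasonal, work-related or caused by repeated self-monitoring, enters the mean difference and would be read as an effect of the VR session.

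At stake are the precision of the follow-up results and, more seriously, their interpretation in a single-cohort study.

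**Working it through.** **1. The plan's own figure.** Sample Size gives SD 9.86, correlation 0.75, difference 3.13, two-sided 5% and 90% power. The SD of the difference is 9.86 × √(2 × (1 − 0.75)) = 6.97. Noncentral-t power is 0.899 with 54 pairs and 0.905 with 55, so the stated 55 reproduces. With 70 pairs, power is 0.959. That calculation is sound and is not questioned here.

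**2. Occasions (Table 1 over 2 + 12 weeks, the minimum).** The unused share with one pair is 1 − 2/total.

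| Scale | Pre | Post | Total | Unused |
|---|---|---|---|---|
| SUDS | 6 | 36 | 42 | 95% |
| GAD-2, PHQ-2, MIOS-4, UCLA-3 | 4 | 24 | 28 | 93% |
| GAD-7, PHQ-9, brief MIOS | 2 | 12 | 14 | 86% |

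**3. Precision of a period-mean contrast.** Under compound symmetry with correlation ρ, the variance with a baseline and b follow-up occasions is proportional to (1 − ρ)(1/a + 1/b), against 2(1 − ρ) for one pair. The SE ratio is therefore √((1/a + 1/b)/2), whatever ρ is:

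- 6 and 36 occasions: 0.31
- 4 and 24 occasions: 0.38
- 2 and 12 occasions: 0.54

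On the MIOS metric with n = 70, the SE for a weekly scale falls from 0.83 to 0.45.

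Serial correlation shrinks the gain. The comparison is then last baseline against last follow-up occasion, and both structures are assumptions:

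- Person-level correlation 0.5 to 0.6 plus lag-1 residual correlation 0.4 to 0.5 between successive occasions: ratios 0.44 to 0.65.
- Correlation 0.5 + 0.5 × exp(−lag/τ), τ of 2 to 4 weeks: ratios 0.64 to 0.67 (variance 41% to 45%).

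**4. Pairs lost.** If each of the two chosen occasions is completed independently with probability 0.9, 0.8 or 0.7 (assumed), then 100 × q² gives 81, 64 or 49 pairs per 100 participants.

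**5. Drift with no VR effect, MIOS metric only.** An assumed 0.2 points per week is 0.2 × 12 = 2.4 points over 12 weeks. With SD of difference 6.97, the paired test declares this significant in 81% of studies with 70 pairs and 92% with 99. A total drift of 1 point gives 22% and 29%, against a nominal 5%.

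Averaging does not cure this. The two period means are centred about 1 week before and 6 weeks after the session, so 7 × 0.2 = 1.4 points of drift remain, now measured against a smaller SE.

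**6. Can a slope-and-step model separate drift?** I took a baseline slope, a step at the session and a slope change after it, under compound symmetry without a random slope. The SE of the step relative to a single pair is about 0.6 for SUDS, 0.8 to 0.9 for twice-weekly scales and 0.9 to 1.2 for weekly scales, depending on where occasions fall relative to the session. The week-12 contrast against the extrapolated baseline line has an SE about 6.5 times (SUDS) to 13 times (weekly scales) the single-pair SE.

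**The case against.** The strongest reply is that the text does not fix one pair. Pre and post are undefined for these scales, and averaging each period before pairing would fit the wording. That stands: a reader might infer that single occasions will certainly be used, and the article does not say so. Averaging would answer most of the lost-data and lost-pair points, but it has no time term either.

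Other tempting readings also go too far:

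- **That the data are discarded from the study.** They feed the prediction and digital-phenotype models in the Personal Digital Phenotype Profile section. They are unused only in the effect test, which those models do not replace.
- **That every scale has 42 occasions.** Only SUDS does.
- **That the 81% and 92% figures apply to all scales.** They use pilot MIOS values. GAD-2, PHQ-2 and UCLA-3 each span 6 points, so their SD cannot be much above 3, and 2.4 points would be 40% of the range.
- **That 30% of pairs will be lost, or that distressed nurses will stop responding.** The 30% is a planning assumption for the MIOS calculation. The Results section reports 99 of 100 VR sessions completed and gives no follow-up completion rate.
- **That modelling a step would isolate the VR effect.** Working step 6 shows otherwise at 12 weeks. GAD and PHQ also ask about the last 2 weeks, so early follow-up forms still cover days before the session and blur any step.

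It is also fair that the study claims only preliminary efficacy and openly lists its lack of a control group.

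**Conclusion.** The point holds as a choice of method that should be improved. The only inferential analysis named for the web-platform scales is a pre/post paired test on a series of 14 to 42 occasions. On the natural one-pair reading, 86% to 95% of occasions and all incomplete pairs fall outside it. On any reading, it cannot tell a VR effect from background change.

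Using all occasions would reduce the SE of the baseline-to-follow-up contrast to 0.31 to 0.54 of the single-pair value under compound symmetry, and to roughly 0.44 to 0.67 under the serial correlations assumed here. The drift, completion and correlation values are illustrations, not estimates from the trial.

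The attribution problem comes from the design. With a minimum 2-week baseline and no control group, no model removes it fully, so the wording of the conclusion matters as much as the model.

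**What to change.** - **Main analysis.** For each web-platform scale, replace the paired test with a linear mixed model on all occasions, with a participant random effect and serially correlated residuals. Compare baseline with follow-up, by week or with a post-VR time trend. It keeps participants with partial data and is valid under missing at random.
- **Short forms.** Add Saturday scores for GAD-2, PHQ-2 and MIOS-4 derived from the long forms, so these series have three occasions a week on one metric. UCLA-3 has no Saturday form and stays at two.
- **Sensitivity analysis only.** Fit a model with a time slope and a step at the VR session, stating that the baseline is too short for a 12-week extrapolation and that the GAD and PHQ recall period blurs a step.
- **Interpretation.** Describe the 12-week change as uncontrolled and not attributable to the VR session alone, and extend the Limitations text to say so.

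The cost is analysis wording, modest programming and reliance on model assumptions about correlation and missingness. Data collection and sample size are unaffected.

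### The Shapiro-Wilk check is set on the scale data, while the paired t test relies on the within-person differences, and a significant result switches the hypothesis tested; the effect is usually small

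*Protocol article*

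**What the plan says.** In the protocol article, under Quantitative Data Analysis, the Statistical Analysis section sets one rule for every scale: "For each scale, the prescore and the postscore will be compared using 2-tailed paired" t tests. Two sentences then make that choice conditional. The first is "The normality of all scale data will be assessed using a Shapiro-Wilk test to validate the use of the 2-tailed paired" t test. The second opens with "If the normality test indicates a significant deviation from a normal distribution, the Wilcoxon signed rank test" and makes that test the replacement. The switch is mandatory once the check is significant.

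The within-person differences appear in that section only for description: "the prescore, postscore, and their differences will be summarized using descriptive statistics such as mean (SD) and median (IQR".

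The Sample Size section rests on the mean change. Its calculation is for a paired t test "to compare the means of the prescore and postscore of MIOS using the POWER procedure in SAS", and it adds: "We set the effect size (mean difference between prescore and postscore) to detect at 3.13".

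**The concern.** A paired t test is a one-sample t test on the within-person differences. Its distributional assumption concerns those differences; the prescores and postscores may have any shape. A check on the scores can therefore go wrong in two directions. It can reject because the scores are skewed or coarse although the differences are well behaved, and so drop a sound test. It can also pass although the differences are strongly skewed.

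The switch also changes the question. The t test addresses the mean change. The signed rank test addresses symmetry of the differences about zero, and in its standard form it discards pairs with no change. Under the stated rule, the shape of the observed data decides which question is answered, and different scales may end up with different ones. At stake are the match between the reported test and the quantity that sized the study, and, with skewed change, the error rate for a claim about mean change.

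**Working it through.** **Inputs.** From Sample Size: "the SD of each score was 9.86 and the correlation of pre- and postscores was 0.75"; mean difference 3.13; two-sided alpha 5%; power 90%; 55 pairs needed; 70 pairs expected after 30% dropout. From Results: 99 completed VR sessions. From VR Data Collection: SUDS runs from 0 to 100 in steps of 10. The article gives no distribution for any scale and no MIOS baseline mean, so all shapes below are assumptions.

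**Step 1: the plan's own figure.**
- SD of the difference = 9.86 × √(2 × (1 − 0.75)) = 6.97.
- Standardised difference = 3.13 / 6.97 = 0.449.
- Exact power from the noncentral t: 54 pairs 89.9%, 55 pairs 90.5%, 70 pairs 95.9%, 99 pairs 99.3%.

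The 55 pairs reproduce exactly. They belong to a paired t test on the mean difference.

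**Step 2: how the rule behaves.** Simulation with 3,000 trials per row, n = 70. The score check fires if Shapiro-Wilk gives P ≤ 0.05 for the prescore or the postscore. A, B and D keep SD 9.86 for each score and r = 0.75.
- A: skewed (exponential) person effect, normal errors, so the differences are exactly normal.
- B: normal prescore, skewed change.
- C: SUDS-like, mean 30 and SD 20 before rounding to tens and limiting to 0–100.
- D: bivariate normal.

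| Case | True mean change | Check fires on scores | Check fires on differences | t test rejects | Wilcoxon rejects | Score-based switch rejects | Difference-based switch rejects |
|---|---|---|---|---|---|---|---|
| A | 0 | 93.6% | 5.4% | 5.1% | 5.3% | 5.3% | 5.3% |
| A | 3.13 | 93.7% | 5.5% | 96.1% | 95.0% | 95.1% | 95.9% |
| B | 0 | 36.3% | 97.3% | 5.6% | 22.1% | 11.1% | 21.9% |
| C | 0 | 100% | 99.7% | 5.1% | 5.4% | 5.4% | 5.4% |
| D | 0 | 9.3% | 4.4% | 5.1% | 4.7% | 5.2% | 5.3% |
| D | 3.13 | 10.2% | 4.7% | 95.4% | 94.6% | 95.3% | 95.3% |

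The Monte Carlo standard error near 5% is √(0.05 × 0.95 / 3000) = 0.4 percentage points.

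- In A the score check drops a valid t test in about 94% of trials, at a power cost of 96.1 − 95.1 = 1.0 point.
- In B it stays silent in 100 − 36.3 = 63.7% of trials although the differences are skewed. When it does fire, it moves to a test that rejects a zero mean change 22.1% of the time.
- In C the switch is close to automatic, whichever variable is checked.
- In B, moving the check to the differences raises rejection from 11.1% to 21.9%. The data-driven change of hypothesis therefore remains wherever the check is placed.

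**Step 3: the MIOS, the scale that was sized.** Integer MIOS-like scores with SD 9.86 and r = 0.75, on an assumed 0–56 range. The score check fired in about 8% of trials at an assumed baseline mean of 28, 10–35% at 20, 57–99% at 15 and about 100% at 10 (n = 70 or 99). Across these runs the switching rule had type I error of 4.6–6.2% and power within about 1 point of the t test.

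**Step 4: a constructed worst case.** Let 20% fall by 12 points and 80% rise by 3: 0.2 × (−12) + 0.8 × 3 = 0, so the mean change is zero. The fixed t test rejects in about 5–6% of trials. The switching rule rejected in anything from 7% to 62%, depending on the prescore shape, noise and sample size assumed.

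**The case against.** The strongest reply has four parts.

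- **The differences may be covered.** A reader might infer that the plan excludes the differences from the check. It does not say so. The wording is broad, the section lists the differences beside the two scores, and the stated purpose is to validate the paired test. An analysis plan that is not shown may name the variable. This stands as a limit on the wording of the point. It does not remove the point: on the inclusive reading the scores are still tested and can still trigger the switch.
- **The t test may well survive for the MIOS.** A reader might infer that the test used for sizing will rarely be run. The article does not support that. The answer runs from about 8% to about 100% switching, depending on an unstated baseline. Near-certain switching can be argued only for coarse or floor-limited scales such as SUDS.
- **Switching usually costs little.** This stands. With roughly symmetric differences, error and power hardly change. A reader might take the worst-case inflation as an expected false-positive rate, but nothing in the article suggests such a response pattern, and the figure moves widely with the assumptions.
- **The rule is prespecified and common, and a rank test suits short ordinal scales.** This is fair for PHQ-2, GAD-2 and UCLA-3, and mean changes are to be summarised anyway. It supports reporting a rank test. It does not support letting a normality test on scores choose the hypothesis.

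The article also claims only preliminary utility, and its Limitations section says that the video's acute efficacy is not the primary aim. That lowers the stakes but leaves the rule as stated.

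**Conclusion.** The point holds in a limited form. The stated rule ties the validity of the paired t test to the scale data, when the relevant quantity is the within-person difference. It then makes the hypothesis depend on the outcome of that check. A score check can drop a sound t test, can miss skewed differences, and can move the analysis away from the mean difference on which 55 pairs were calculated.

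The size is modest. The sample size is unaffected. Type I error stays near 5% and power changes by about 1 point when the differences are roughly symmetric. Rejection under zero mean change is inflated only when the differences are strongly skewed: 11.1% for the score-based switch against 5.6% for the fixed t test in the assumed case B, with more extreme values only in a constructed example. All firing and rejection rates rest on assumed distributions. Two things do not rest on them: which variable the t test depends on, and the fact that the switch changes the quantity tested. It is worth correcting because the fixed t test stayed between 5.1% and 5.6% under zero mean change in all four assumed cases at 70 pairs, so the switch brought no gain there.

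**What to change.** Replace the two conditional sentences in the Statistical Analysis section with, for example: *For each scale, the within-person change will be analysed by a two-sided paired t test and reported as a mean difference with 95% confidence interval. The distribution of the differences will be inspected by plot. A Wilcoxon signed rank test will be reported as a sensitivity analysis and will not replace the t test.*

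Redirecting Shapiro-Wilk to the differences while keeping the switch is not enough, because the data would still choose the hypothesis.

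The cost is a few sentences, with no new data and no change to the 55-pair calculation. The drawback is that some would prefer a rank test as the main result for the coarse short scales; the sensitivity analysis supplies it. Because the article reports that data collection has ended, the change should be dated, with a statement of whether outcome data had been seen when it was made.

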#### VR Data Collection

A visual overview of the data collection process during the VR simulation is shown in Figure 3.

A total of 4 scales and one short-form scale will be used to collect self-reported data during the session. The Moral Injury Outcome Scale (MIOS) [46] is used to assess an individual’s reaction to a potentially morally injurious event and is indexed to the most morally distressing experience of their life that currently distresses them. While the VR simulation is intended to simulate moral distress, the MIOS is designed to assess moral injury and, as such, is used as a proxy of our intended measure. This study will use the clinical version of the brief MIOS (Multimedia Appendix 2), which consists of 14 questions that assess an individual’s thoughts and feelings in response to a distressing event and eight items that assess how the event has impacted their daily life. The scale was adapted for nursing professionals by the research team in collaboration with the creator of the scale. Additionally, we will use a shortened version, termed the MIOS-4 (Multimedia Appendix 2), which contains the 4 items from the MIOS with the largest variance. The purpose of the MIOS during the VR session is 2-fold: first, it is used to characterize preexisting moral injury symptoms in participants. Second, the content of the scale is leveraged to assess acute reactions to the simulated moral dilemma.

The Subjective Units of Distress Scale (SUDS) [47] measures the level of distress an individual is experiencing at the moment. Individuals rate their current level of anxiety or discomfort on a scale of 0 to 100, in intervals of 10. The purpose of administering this scale is to obtain a general measure of acute distress elicited by exposure to a moral dilemma.

The Igroup Presence Questionnaire Scale [48] measures an individual’s sense of presence and reality during the VR session. This scale is used to assess the VR quality and user experience.

The Virtual Reality Sickness Questionnaire [49] assesses common side effects after VR exposure. This scale will be used to assess the safety and tolerability of the VR simulation.

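### One P≤0.05 rule covers a pre-post test on every scale, and the MIOS comparison that sized the trial is neither fully specified nor designated primary in the analysis

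*Protocol article*

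**What the plan says.** Protocol article, Statistical Analysis: "For each scale, the prescore and the postscore will be compared using 2-tailed paired" *t* tests, with the Wilcoxon signed rank test if normality is rejected. The brief MIOS is named first, with MIOS-4 and SUDS as examples of other VR-session scales. Similar analyses are then promised for the platform scales, with GAD-7, GAD-2, PHQ-9, PHQ-2 and UCLA-3 as examples. The section ends: "Results will be considered significant with a" P value of 0.05 or less. It does not separate primary, secondary and exploratory tests.

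Protocol article, Sample Size: the calculation is for one paired comparison of MIOS prescore and postscore. "A sample size of 55 pairs (55 patients) was estimated" on these inputs: "the SD of each score was 9.86 and the correlation of pre- and postscores was 0.75"; "We set the effect size (mean difference between prescore and postscore) to detect at 3.13". With 30% dropout from 100, the plan expects 70 pairs.

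On nesting, VR Data Collection describes the MIOS-4 as a short form "which contains the 4 items from the MIOS with the largest variance". PHQ Scale says "The PHQ-2 includes only the first 2 items of the PHQ-9". The GAD Scale section says the same of GAD-2 and GAD-7 (items 1 and 2).

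**The concern.** The trial was sized for one test at 5%, but the decision rule lets any of about 11 tests be called significant at 5%. The Participants section says the sample is recruited to determine preliminary efficacy, so a significant improvement on any scale could be read as support for the digital suite.

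Two features make this worse. First, the word MIOS in the Sample Size section does not identify a contrast. There are two versions (brief MIOS and MIOS-4) in two settings (VR session and platform), so at least four contrasts could later be presented as the powered one, before any choice of time points. Second, three short forms are tested beside the scales that contain their items. A chance movement in those items can appear as two positive outcomes.

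**Working it through.** **1. The plan's own figure.** SD of the paired difference = 9.86 × √(2 × (1 − 0.75)) = 6.97. Standardised effect = 3.13 / 6.97 = 0.449. With the noncentral *t* distribution, two-sided α 0.05:

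| Pairs | Power |
|---|---|
| 54 | 89.9% |
| 55 | 90.5% |
| 70 | 95.9% |

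The stated 55 pairs, and power above 90% at 70 pairs, both reproduce.

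**2. Number of tests.** VR session: brief MIOS, MIOS-4, SUDS = 3 (Statistical Analysis). Platform: brief MIOS, MIOS-4, SUDS, GAD-7, GAD-2, PHQ-9, PHQ-2, UCLA-3 = 8 (Additional Scales and Table 1). Total 11. This count is an assumption: both lists in Statistical Analysis are given as examples, and only five of the platform scales are named there. More time points would raise it.

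**3. Chance of a false positive if no scale changes.** If the tests are independent:
- any significant result: 1 − 0.95^11 = 43.1%
- a significant improvement, with 0.025 per test in that direction: 1 − 0.975^11 = 24.3%

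The document gives no correlations between scales, so a range is assumed. Simulation of 11 equally correlated normal test statistics gives:

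| Assumed correlation | Any significant result | At least one false improvement |
|---|---|---|
| 0 | 43% | 24% |
| 0.3 | 37% | 19% |
| 0.5 | 30% | 15% |
| 0.7 | 22% | 11% |
| Single test, for reference | 5% | 2.5% |

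A less uniform structure (0.3–0.7 within a setting, 0.85–0.9 between short and long form, 0–0.4 across settings) gives about 24–35% for any significant result, inside the same range. The expected number of false positives is 11 × 0.05 = 0.55 whatever the correlation.

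**4. Nesting.** With an assumed short-to-long correlation of 0.85–0.90, when the long form is significant by chance, its short form is also significant 51–59% of the time. High correlation also means that the short forms add less to the overall error rate than unrelated scales would. Their harm lies in double reporting.

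**5. What a repair does to power for the 3.13-point MIOS difference.**

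| Option | α for MIOS | Power at 70 pairs | Pairs for 90% |
|---|---|---|---|
| One primary test | 0.05 | 95.9% | 55 |
| Bonferroni over 11 | 0.05/11 = 0.0045 | 79.1% | 89 |

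At 99 pairs, Bonferroni over 11 would give 93.8%. However, the Results section reports 99 completed VR sessions, not 99 complete follow-up pairs, so that figure could apply only to a VR-session contrast.

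**The case against.** Several points can be made for the plan.

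- **There is an implicit primary.** Only pre-post MIOS is powered, and the brief MIOS is named first in the analysis. This stands in part: a reader might infer that the trial has no primary comparison at all, which goes too far. But the analysis text gives that comparison no priority, and the contrast is not identified.
- **A false efficacy signal is not likely.** A reader might infer that one is more probable than not. The figures do not support this: all lie below one half, and the share that would look like improvement is 11–24%. Substantially inflated is the accurate description.
- **The same answers are not scored twice on the platform.** Table 1 gives the short forms on Monday and Thursday and the long forms on Saturday. This stands. Still, GAD and PHQ each ask about the last 2 weeks, so forms given days apart cover largely the same period and share items.
- **The article is condensed, and an analysis plan may exist.** Missing multiplicity detail alone would be no finding. Here, however, the article states a positive rule for all results, which an analysis plan would have to override.
- **The study is a preliminary single cohort.** The Limitations section concedes the lack of a control group and says the video's acute efficacy is not the primary aim. This lowers the severity and makes formal adjustment of every scale debatable. It does not justify a blanket significance rule, and the supplied text does not say which aim or outcome is primary.

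**Conclusion.** The point holds in a limited form. As written, the plan calls any of about 11 pre-post tests significant at P≤0.05 and carries no priority over from the MIOS comparison that sized the trial, whose version, setting and time points are not fixed. If nothing changes, the chance of at least one significant result is about 22–43%, roughly 4 to 9 times the nominal 5%. The chance of at least one false improvement is about 11–24%, against 2.5%.

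These ranges rest on the count of 11 and on assumed common correlations from 0.7 down to 0. The sample size itself is sound on its stated inputs. The nested short forms matter mainly because one chance result can look like two.

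**What to change.** In Sample Size and Statistical Analysis, name one MIOS version, one setting and one pre/post time-point pair as the single primary test at two-sided 0.05. Confirm that the SD of 9.86, the correlation of 0.75 and the 3.13-point difference refer to that version.

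Replace the blanket P≤0.05 rule for all other scales: label them exploratory, or adjust them, for example by Holm. For a preliminary study either is defensible. State that MIOS-4, GAD-2 and PHQ-2 do not count as separate evidence beside their parent scales.

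The cost is a short change of text and no added sample size: 55 pairs still give 90% power. The downside is that the other scales can no longer each support a stand-alone efficacy claim.

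Timing matters. The Results section says data collection was completed in December 2023. The designation should be made and dated before the outcome data are analysed; if they have already been analysed, it must be disclosed as post hoc.
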